***Study Within a Trial (SWAT)***

Relying on a text-heavy PIS has become the norm for many trials. There is conflicting evidence that introducing infographics (visual representations of information) has the potential to improve the participant experience [38, 39, 40].

A methodological Study Within a Trial (SWAT) will be embedded within BASIL+ to evaluate the effectiveness of a single page infographic, to go alongside the PIS, on participant recruitment and response rates. The infographic displays a participant’s journey through the BASIL^+^ trial. The use of the infographic will be tested in a cluster RCT embedded within the BASIL^+^ trial. Study sites (n=12 approx.) will be randomised 1:1 using simple randomisation to either the SWAT intervention group (potential participants receive PIS as usual, and infographic) or the SWAT control group (potential participants receive PIS as usual, and no infographic). Generation of the SWAT allocation sequence will be undertaken independently by a statistician at YTU not involved with the BASIL^+^ recruitment process. Study sites will be blind to SWAT group allocation.

The primary outcome of the embedded SWAT will be the participant recruitment rate into the BASIL^+^ trial. Secondary outcomes will be i) participant response rate in terms of expressions of interest in BASIL+ (permission to contacts received, direct participant contacts, or participant completion of the online consent form – see recruitment section above), and ii) retention in BASIL+ as measured by response to the three month post-randomisation participant questionnaire.

The proportion of participants randomised into the BASIL^+^ trial will be compared between the SWAT groups using a logistic regression model, adjusting for trial site as a random effect. The secondary outcomes will be similarly analysed; the model for response rate at the three-month follow-up will also include a covariate for BASIL+ allocation (intervention/usual care/not randomised). A simple cost analysis will be conducted to estimate the cost per extra participant recruited associated with the infographic.

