***Sample size***

For populations with case-level depression, a successful treatment outcome has been defined as 5 points on the PHQ9 [41]; however, this was calculated using distribution methods, which are not currently advocated [42], and does not incorporate our wider population of interest. In an older population with subthreshold depression a difference of 1.3 has been found to be clinically and cost-effective [43] with a standard deviation of 4, equating to a standardised effect size of 0.325. An effect size of 0.3 is assumed for this calculation, which is also in line with pooled standardised mean differences found in a meta-analysis of previous trials of collaborative care [44]. Assuming 90% power, 5% alpha, 0.3 effect size and 20% attrition (from mortality and loss to follow-up) the trial would need to randomise 590 participants. However, this calculation is very conservative. In the primary analysis, baseline PHQ9 score shall be included as a covariate, which will result in gains in power. Therefore, accounting for the correlation between baseline and outcome PHQ9 score can reduce the required sample size. In the external pilot trial, a correlation of 0.58 was observed between the PHQ9 score at baseline and three months amongst participants who scored ≥5 at baseline, and follow-up at three months was 90% [23]. Assuming a correlation of at least 0.5, 90% power, 5% alpha, 0.3 effect size and 10% attrition, 392 participants would need to be recruited and randomised into the trial. Calculations conducted using Stata v15.

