***Statistical analyses***

A detailed statistical analysis plan will be produced prior to data analysis and approved by the joint Programme Steering and Data Monitoring and Ethics Committee. Analysis will be conducted on an intention to treat basis, using two-sided statistical tests at the 5% significance level, using Stata v17 or later. The statistician will not be blinded to treatment allocation.

The flow of participants through the trial will be detailed in a CONSORT diagram [Figure 2]. The number of individuals screened, eligible and randomised will be presented, with reasons for non-participation provided where available. Intervention adherence will be recorded and reported, including the number of sessions completed. The number of participants withdrawing from the intervention and/or the trial and any reasons for withdrawal will be summarised by trial arm.

Participant baseline data will be summarised descriptively by trial arm, for all randomised participants and for all who are included in the primary outcome analysis. No formal statistical comparisons will be undertaken on baseline data. Continuous measures will be reported as means and SD, while the categorical data will be reported as counts and percentages.

The primary outcome (PHQ9) will be analysed using a linear mixed model, incorporating data from all post-randomisation follow-up time points (one, three and 12 months). The model will include time, trial arm, an arm-by-time interaction, and baseline PHQ-9 score as fixed effects, with participant nested within site as random effects. The model will provide an overall treatment effect over time as well as estimates at individual time points, which will be reported as mean differences, 95% confidence intervals and p-values. The primary time-point of interest is pre-specified at three months.

The secondary outcomes of GAD7, De Jong Gierveld Scale, Lubben Social Network Scale, and SF-12v2 (mental and physical health component scores separately) will be similarly analysed.

A complier average causal effect (CACE) analysis will be conducted for the primary outcome to account for non-compliance with the intervention.

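### With about 12 randomised sites and no small-sample correction, the SWAT recruitment comparison would reject falsely about 8% to 12% of the time under usual Wald inference, if sites differ modestly or more

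*Protocol*

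**What the plan says.** The protocol's section Study Within a Trial (SWAT) sets the design: "The use of the infographic will be tested in a cluster RCT embedded within the BASIL^+^ trial". On allocation it says: "Study sites (n=12 approx.) will be randomised 1:1 using simple randomisation". On the outcome: "The primary outcome of the embedded SWAT will be the participant recruitment rate into the BASIL^+^ trial". The proportions randomised "will be compared between the SWAT groups using a logistic regression model, adjusting for trial site as a random effect".

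The secondary outcomes are expressions of interest and response to the three-month questionnaire. Of these it says: "The secondary outcomes will be similarly analysed". The three-month model adds a covariate for BASIL+ allocation. A simple cost analysis gives the cost per extra participant recruited.

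The SWAT section names no estimation method, test, reference distribution, degrees of freedom, ICC or significance level. The only level in the protocol is the general one under Statistical analyses: "using two-sided statistical tests at the 5% significance level, using Stata v17 or later".

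**The concern.** The model respects the unit of randomisation. The difficulty is the number of units. Everyone at a site gets the same SWAT allocation, so the infographic effect is judged against variation between sites, and about 12 sites leave about 10 degrees of freedom to estimate that variation. More invitations per site do not add any.

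A standard random-intercept logistic fit by maximum likelihood tends to underestimate the between-site variance with so few clusters. The Wald z-test then treats that estimate as if it were known. Both faults make the interval too narrow. A chance difference between two small groups of sites could then be reported, and costed, as an effect of the infographic. The protocol itself describes the existing evidence on infographics as conflicting, so a spurious result would do harm.

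**Working it through.** **Inputs from the protocol.** About 12 sites, simple 1:1 randomisation, random-effect logistic regression, general two-sided 5% level, and a recruitment target: "0.3 effect size and 10% attrition, 392 participants would need to be recruited and randomised into the trial". The SWAT has no sample size or power of its own to reproduce. The target is used only to size the sites, and it does reproduce: 2 × (1.960 + 1.282)² / 0.3² gives 234 per arm; 234 × (1 − 0.5²) = 175.5, so 176 per arm; 352 / 0.9 = 391.1, so 392. Then 392 / 12 is about 33 randomised per site.

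**Assumptions not in the protocol.** Either 3% of 1,100 or 10% of 330 invited patients are randomised at each site (33 in both cases). Site sizes are equal or have a coefficient of variation of 0.5. The latent-scale ICC runs from 0 to 0.1, with site SD on the logit scale = √[ICC/(1 − ICC) × π²/3].

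An ICC of 0.01 gives a site SD of 0.182. Around a 3% mean, plus or minus 2 SD is recruitment of about 2.1% to 4.3% across sites, which is modest variation.

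**Step 1: closed form, 12 sites split evenly, between-site variance dominant.** Maximum likelihood divides the between-site sum of squares by 12 instead of 10, so z = t₁₀ × √(12/10).
- ML variance, z-test: P(|t₁₀| > 1.96 × √(10/12)) = P(|t₁₀| > 1.789) = **10.4%**. With 10 sites it is 11.8%, and with 14 sites 9.5%.
- Likelihood-ratio test: reject when 12 × ln(1 + t²/10) > 3.84, that is |t₁₀| > 1.942, giving **8.1%**.
- Unbiased variance, z-test: P(|t₁₀| > 1.96) = **7.8%**.
- The correct critical value is 2.228. Since 2.228 / 1.789 = 1.245, the ML Wald interval would need to be about 25% wider.

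**Step 2: simulation with no infographic effect.** Random-intercept logistic model by maximum likelihood with adaptive quadrature, 12 sites, 1,500 to 2,000 runs per scenario. At a true 10%, the simulation standard error with 2,000 runs is √(0.1 × 0.9 / 2000) = 0.7 percentage points.

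| Outcome and ICC | Wald z | Likelihood ratio | Site-level t, 10 df |
|---|---|---|---|
| Recruitment, 0 to 0.002 | 4.3%–6.4% | 3.7%–5.6% | 4.0%–4.6% |
| Recruitment, 0.005 | 7.7%–8.8% | 6.0%–7.2% | 4.3%–5.5% |
| Recruitment, 0.01 | 8.7%–11.1% | 6.9%–9.0% | 4.4%–5.2% |
| Recruitment, 0.03 to 0.1 | 10.0%–11.8% | 7.5%–9.6% | 4.2%–5.9% |
| Retention (33 per site, 90%), 0.01 | 4.6% | 5.0% | 4.1% |
| Retention (33 per site, 90%), 0.05 | 7.0% | 6.2% | 4.5% |

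A second simulation used 1,000 invited per site, 3.3% recruited and site SD 0.3 or 0.5. It gave 9.0% and 10.7% for the Wald test, against 4.0% and 5.3% for the site-level t-test.

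**Step 3: uneven allocation.** Under simple randomisation of 12 sites, a 3:9 or more uneven split has probability 2 × (1 + 12 + 66 + 220) / 4096 = 14.6%. A simulated 3:9 split gave 9.6% for the Wald test and 4.7% for the site-level t-test.

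**Step 4: would a t reference alone be enough?** Keeping the ML mixed model but using t₁₀ gives 4.3% to 8.4% for recruitment at ICC 0.005 or more. That helps, but the variance bias remains.

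**The case against.** The strongest reply is that the protocol fixes only a class of model. Mixed logistic regression is a recognised analysis of a cluster trial, and the protocol names no Wald z-test. A separate analysis plan is promised and could add a small-sample method without contradicting the protocol. That stands: the rates above describe what follows if the stated model is fitted with its usual inference, not a test that the protocol prescribes. It does not dispose of the point, because the protocol does choose the model, the choice suits many clusters better than 12, and nothing in the text signals a correction.

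The size also depends on an ICC that the protocol does not give. This stands too, which is why the result is a range with its conditions attached.

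Four stronger readings are tempting but unsupported:
- That every SWAT outcome has double the error rate. Retention is nominal to about 7%.
- That the cost result has too narrow an interval. The protocol describes a simple cost analysis with no interval or test; the risk is only that a chance difference gets costed.
- That the SWAT section itself promises 5%. The level is stated for the trial's analyses in general.
- That the main trial is affected. It is not.

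Finally, a plain site-level t-test cannot carry the allocation covariate that the protocol requires for three-month response. This is correct, and the fix below allows for it.

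**Conclusion.** The point holds for the SWAT recruitment comparison, conditionally. With about 12 sites, maximum-likelihood fitting and a Wald z-test, the false-positive rate is about 8% to 12% if the latent ICC is about 0.005 or more, and *roughly double* is fair from about 0.01. With a likelihood-ratio test it is about 6% to 10%. If sites hardly differ (ICC 0 to 0.002) it is near nominal. Expressions of interest share the structure of the recruitment outcome, so the same reasoning applies, but that outcome was not simulated separately.

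The figures rest on assumed numbers invited, recruitment percentages and ICCs. The closed form needs only the number of sites, an even split and dominant between-site variance. The matter is confined to a methodological sub-study and should be settled before the SWAT data are analysed.

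**What to change.** For recruitment and expressions of interest, specify a cluster-level analysis: a t-test on site log-odds or site proportions with number of sites minus 2 degrees of freedom. A permutation test over the possible site allocations is an alternative.

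For three-month response, use a two-stage cluster-level analysis on site residuals adjusted for BASIL+ allocation. Alternatively, keep the mixed model with REML-type variance estimation and a t reference with sites minus 2 degrees of freedom. If log-odds are used for that outcome, state a continuity correction: with 33 per site and 90% retention, a site has no non-responders with probability 0.9³³, about 3%.

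The cost is a few sentences in the analysis plan, wider intervals (about 25% wider than the ML Wald interval where between-site variance dominates) and slightly more analysis work. No new data are needed.

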***Safety considerations***

A risk management protocol will be followed during all participant contact. Risk assessment training and standard operating procedures will be provided to all researchers and BSWs. Clinical members of local study teams will support the assessment of risk and communication of risk information to a participant's GP or emergency services, as deemed appropriate.

Serious adverse events and adverse events will be monitored for by all researchers and BSWs and reported in a timely manner.

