***Randomisation and blinding***

Following baseline questionnaire completion, eligible and consenting participants will be randomised 1:1 to either receive the intervention (BA) or usual care with signposting information. Randomisation will take place via a secure online randomisation service provided by the York Trials Unit (YTU). A YTU statistician not involved with participant recruitment will generate the allocation schedule, using block randomisation stratified by site with randomly varying block sizes. Participants will be informed of their group allocation by telephone (and confirmed by letter). The participant’s GP will be informed by letter of the participant’s group allocation; this will include information about the participant’s mood symptoms (with the participant’s consent).

Researchers completing follow-up questionnaires (outcome measures) with participants over the telephone will be blind to group allocation. Due to the nature of the intervention, it is not possible to keep participants or the BASIL^+^ Support Workers delivering the intervention blind to allocation.

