Participants will be offered up to eight intervention sessions, delivered by a trained BSW and supported by the self-help booklet. The self-help booklet has been developed over a number of similar studies; most recently during the BASIL-C19 pilot study [23], where it was adapted for use during the COVID-19 pandemic with help and feedback from older adults, BSWs and a range of stakeholders, including members of the existing MODS/BASIL Patient and Public Involvement (PPI) group. Further minor adaptations were made for BASIL^+^ following the BASIL-C19 pilot (including minor design and wording changes to the self-help booklet). All sessions will be delivered remotely, either over the telephone or by video call (where this is available and preferred) and according to participant preference. The first session will last approximately one hour with subsequent sessions lasting approximately 30 minutes.

The depression scale of the Depression Anxiety Stress Scale (DASS) [30] will be used as a within session depression symptom monitoring tool. The DASS is a widely used and simple to score monitoring tool with clear clinical cut off scores (non/mild/moderate/severe). DASS scores will be used to aid decision making by BSWs in conjunction with their BASIL^+^ clinical supervisor. Where risk or significant clinical deterioration is indicated the participant will be supported to access more formal healthcare interventions.

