***Comparator***

Participants allocated to the usual care with signposting information group will receive their usual care as provided by their current NHS and/or third sector providers. In addition, usual care (control) participants will be signposted to sources of self-help and information, including advice on how to keep mentally and physically well. Examples of such sources includes guidance from UK Health Security Agency (UKHSA), previously known as Public Health England [31], and Age UK [32].

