***Outcome measures***

Data will be obtained at baseline and one, three, and twelve months post-randomisation. Baseline data will be collected over the telephone with a researcher. Participants will be offered the option to complete follow-up questionnaires online, via a secure emailed link, or over the telephone with a researcher. A reminder system including emails and letters will be in place to use where appropriate.

The primary outcome will be self-reported depression severity (as measured by the PHQ9) [29] at three months post-randomisation.

Secondary outcomes will include depression (PHQ9) [28] at one and twelve months, and loneliness (De Jong Gierveld Scale – 11 items) [33]; social isolation (Lubben Social Network Scale - 6 items) [34]; anxiety (GAD7) [35]; and health related quality of life (SF-12v2 [36] and EQ-5D-3L [37]) at one, three and twelve months post-randomisation. A bespoke questionnaire will be used to collect health service use data at all time-points. Information regarding COVID-19 circumstances will be collected at all-time points.

Demographic information will be collected at baseline, to include age, LTC types/health condition(s), socio-economic status, ethnicity, education, cohabitation status, number of children.

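### Adverse events are captured by support workers who see only the intervention arm, so a table by arm that pools their reports is liable to over-count events in that arm

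*Protocol*

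**What the plan says.** Protocol, Safety considerations, gives the only event-capture rule in the document: "Serious adverse events and adverse events will be monitored for by all researchers and BSWs and reported in a timely manner". 

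The intervention section describes the BSWs' contact with participants: "Participants will be offered up to eight intervention sessions, delivered by a trained BSW and supported by the self-help booklet". It also has the BSWs track depressive symptoms inside sessions with the DASS depression scale and act on signs of risk or deterioration. 

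The Comparator section describes no BSW contact for controls. Besides usual care, "usual care (control) participants will be signposted to sources of self-help and information, including advice on how to keep mentally and physically well". 

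The scheduled assessments common to both arms are in Outcome measures: "Data will be obtained at baseline and one, three, and twelve months post-randomisation". On how they are completed: "Participants will be offered the option to complete follow-up questionnaires online, via a secure emailed link, or over the telephone with a researcher". 

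On blinding, Randomisation and blinding says: "Researchers completing follow-up questionnaires (outcome measures) with participants over the telephone will be blind to group allocation". For the other group that captures events, "it is not possible to keep participants or the BASIL^+^ Support Workers delivering the intervention blind to allocation". 

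Statistical analyses lists no between-arm comparison of adverse events.

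**The concern.** One of the two capture routes exists in one arm only. An intervention participant may mention a fall, an admission or worsening mood to a BSW in any of up to eight live sessions. A control participant has only the common follow-ups. If those are done online, a control may have no scheduled live follow-up contact, while an intervention participant who also goes online still has the sessions. 

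The routes differ in kind as well as number. BSW capture is unblinded and comes with structured symptom monitoring, so psychological deterioration is looked for more often in one arm. Telephone follow-up is blinded and applies to both. 

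A count by arm that pools the two routes therefore reflects opportunity to report as well as harm. A spurious excess could be read as harm from the intervention, or a true excess could be waved away as ascertainment. The Protocol as shown describes no source field, no common event question and no matched capture for controls that would let a reader tell these apart.

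**Working it through.** The Protocol gives no event rate, capture rate or safety figure, so there is no figure of its own to reproduce. Its sample size has no bearing on this point.

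**Scheduled contacts after randomisation**
- Control: 3 (months 1, 3 and 12).
- Intervention: 3 + up to 8 = up to 11.
- Maximum ratio: 11/3 = 3.7. Adding the telephone call that tells every participant the allocation gives 12 v 4, a ratio of 3.0. The gap of eight is unchanged.

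This is a ratio of opportunities, not of events.

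**Model for the reported risk ratio, with no true difference**
- p = true risk, the same in both arms.
- r = proportion of events captured at the common follow-ups, the same in both arms.
- b = proportion of the remaining events captured by BSWs.
- Reported risk, control: p·r.
- Reported risk, intervention: p·[r + (1−r)·b].
- Spurious ratio: 1 + b(1−r)/r.

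The ratio is 1.00 if r = 1 or b = 0, and above 1 otherwise. An example, all values assumed: p = 10%, r = 0.7, b = 0.5 gives 7.0% in control and 10% × (0.7 + 0.3 × 0.5) = 8.5% in intervention.

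**Allowing for when sessions happen**

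BSWs cannot detect events that occur after sessions end. The Protocol gives no session timetable. Its timeline section has recruitment ending in February 2022 and delivery ending in March/April 2022, which leaves the last recruits roughly one to two months of sessions. Assume, generously, that sessions span 3 of the 12 months and that events occur at a constant rate. A capture of 0.5 during sessions then becomes 0.5 × 3/12 = 0.125 over the whole follow-up.

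| r (assumed) | Session period, b = 0.5 | Full 12 months, b = 0.125 |
|---|---|---|
| 0.8 | 1 + 0.5 × 0.2/0.8 = 1.13 | 1 + 0.125 × 0.2/0.8 = 1.03 |
| 0.6 | 1 + 0.5 × 0.4/0.6 = 1.33 | 1 + 0.125 × 0.4/0.6 = 1.08 |

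**Wider range**
- Session period: from 1 + 0.25 × 0.1/0.9 = 1.03 (r = 0.9, b = 0.25) to 1 + 1 × 0.5/0.5 = 2.00 (r = 0.5, b = 1).
- Full 12 months, same cases with b multiplied by 3/12: from 1 + 0.0625 × 0.1/0.9 = 1.01 to 1 + 0.25 × 0.5/0.5 = 1.25.

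**After the change**

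A comparison restricted to events elicited at the common assessments sets b = 0, and the ratio is 1.00 by this route.

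**The case against.** The strongest reply is that the Protocol plans no between-arm safety comparison. The safety section speaks of monitoring and reporting only, and the choice of events to tabulate belongs to an SAP that is promised but not shown. The full trial protocol listed under Supporting Information and the risk procedures mentioned in the safety section are not shown either, and may already provide a source field or an event question. This stands as a limit on the claim: no stated analysis is wrong. It does not remove the point, because the asymmetry lies in data collection. An SAP can choose among recorded events, but it cannot recover control events that nobody asked about, or separate sources that were not recorded.

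A second reply is that the bias may be small. Sessions end well before 12 months. The 1- and 3-month follow-ups fall early enough to catch many of the same events. The health service use questionnaire, given to both arms at all time-points, may bring some serious events to light equally. Attendance may also be below eight sessions. All of this stands and is why the 12-month figures are modest.

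A third reply is that unequal contact is inherent in testing a contact-based therapy against usual care. That is so, and it is a reason to keep the sources apart rather than to pool them.

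A reader might go further and infer that every between-arm safety comparison in this trial is biased or uninterpretable, or that 3.7 times the contacts means 3.7 times the events. The documents support neither. A comparison of events elicited alike in both arms is free of this mechanism, and contacts do not translate into events at any known rate.

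**Conclusion.** The point holds as a limited one. By design, one capture route operates only in the intervention arm, and it is unblinded. If all reported events are tabulated by arm without regard to source, the count is liable to be too high in the intervention arm. The direction follows from the design.

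The size does not, because r, b and the session period are all assumed here. On the assumptions in the table, the spurious ratio is modest over 12 months (about 1.03 to 1.08) and larger for events within the session period (1.13 to 1.33). It is nil if the common follow-ups capture everything or BSWs add nothing.

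The PHQ9 primary outcome and the sample size are not affected. The point merits action because the remedy is cheap and cannot be fully supplied later by analysis.

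**What to change.** Keep BSW reporting for participant safety, and make four additions:

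1. Record the source of every event (BSW session, telephone follow-up, online follow-up, other).
2. Ask the same event question at the 1-, 3- and 12-month assessments in both arms, in the telephone and online versions alike.
3. Base the between-arm summary on events elicited by that question.
4. List events detected only by BSWs separately, labelled as such.

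The cost is one field on the event form and one item in questionnaires already in use. There are two downsides. The comparative table omits BSW-only events, although they are still reported in the separate list. And since the current version is dated December 2021, with recruitment due to close in February 2022, the new question may reach only the remaining follow-ups. For events already reported, source may still be recoverable from the existing reports and should be back-filled where it is.
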